## Abstract

Diagnostic and treatment strategies for acute coronary syndrome have improved dramatically over the past few decades, but mortality and recurrent myocardial infarction rates remain high. An aging population with increasing co-morbidities heralds new clinical challenges. Therefore, in order to evaluate and improve current treatment strategies, detailed information on clinical presentation, treatment and follow-up in real-world patients is needed. The Future Optimal Research and Care Evaluation in patients with Acute Coronary Syndrome (FORCE-ACS) registry (ClinicalTrials.gov Identifier: NCT03823547) is a multi-center, prospective real-world registry of patients admitted with (suspected) acute coronary syndrome. Both non-interventional and interventional cardiac centers in different regions of the Netherlands are currently participating. Patients are treated according to local protocols, enabling the evaluation of different diagnostic and treatment strategies used in daily practice. Data collection is performed using electronic medical records and quality-of-life questionnaires, which are sent 1, 12, 24 and 36 months after initial admission. Major end points are all-cause mortality, myocardial infarction, stent thrombosis, stroke, revascularization and all bleeding requiring medical attention. Invasive therapy, antithrombotic therapy including patient-tailored strategies, such as the use of risk scores, pharmacogenetic guided antiplatelet therapy and patient reported outcome measures are monitored. The FORCE-ACS registry provides insight into numerous aspects of the (quality of) care for acute coronary syndrome patients.

## 1. Introduction

Over the past decades, the overall mortality of patients admitted with acute coronary syndrome (ACS) has decreased [1,2]. Simultaneously, the implementation of evidence-based treatments in ACS patients has led to a lower risk of recurrent ischemic events [1,2]. However, nationwide registries in different countries have demonstrated that approximately 20–30% of patients have a recurrent cardiovascular event (i.e., myocardial infarction (MI), stroke or cardiovascular death) in the five years following their initial admission [3,4]. For example, a conjoined registry of ACS patients (*n* = 3721) from the United Kingdom and Belgium has shown that one in five ACS patients are deceased within five years, implying that careful monitoring beyond the first year and additional secondary prevention measures are warranted [3].

Accordingly, several steps have been taken to improve secondary prevention. During the past 20 years, the introduction of more potent antithrombotic treatment has been associated with a substantial reduction of ischemic events and improved survival, but at the cost of an increase in bleeding events [5]. More recently, new patient-tailored Dual AntiPlatelet Therapy (DAPT) strategies have been developed, such as the use of risk scores to guide DAPT duration after ACS, potentially allowing for a better assessment of bleeding and thrombotic risk in individual patients [6]. For example, the PREdicting bleeding Complications In patients undergoing Stent implantation and subsEquent Dual AntiPlatelet Therapy (PRECISE-DAPT) score and the DAPT score are promising tools for personalized decision-making regarding the optimal duration of DAPT [7,8]. However, a necessary prospective validation of strategies incorporating these scores has not yet been performed. In addition, preventive strategies have often arisen from large randomized controlled trials (RCTs). While RCTs have a high internal validity, they might not reflect the patient population in daily clinical practice. For example, women, older patients and patients with a bleeding history are underrepresented in most RCTs, possibly influencing the value of the outcome of RCTs for the elderly [9]. In contrast to most RCTs, registries have less strict inclusion criteria (e.g., no age limit and no limitations on comorbidities) and therefore better reflect the real-world population [10,11,12,13,14].

Furthermore, different regional treatment protocols co-exist for patients with ACS, leading to a wide variety in treatment between hospitals. Currently ongoing nationwide registries gain insight into cardiac treatment strategies and intend to improve the quality of care, but are often limited, using minimal datasets for data collection where important details on treatment are lacking, such as antithrombotic treatment strategy (type, duration and compliance) and both ischemic and bleeding end points during follow-up. In this manuscript, we describe how the FORCE-ACS (Future Optimal Research and Care Evaluation: Towards “personalized medicine” in patients with Acute Coronary Syndrome in daily clinical practice) registry allows the monitoring of ACS patients across the Netherlands and overcomes some of the limitations of previous registries. To illustrate the scope of research projects conducted within the registry, we will elaborate on the study design of the project, evaluating the effects of risk score-guided DAPT duration.

## 2. Methods

### 2.1. Study Objectives

The primary objectives of the FORCE-ACS registry are: (1) to create an ongoing registry of patient characteristics and treatment strategies, therefore facilitating future research, enabling personalized therapy and aiming to improve quality of care for patients with ACS; (2) to assess the efficacy and safety of new drugs or strategies versus the current treatment and, if available, to compare the results of these novel treatments in daily practice to RCTs; (3) to evaluate and improve current health care pathways between different Dutch hospitals (e.g., the collaboration between interventional and non-interventional cardiac centres), which can also be used for value-based health-care initiatives; and (4) to increase the adherence to current guidelines to improve secondary prevention. All data needed for mandatory quality-of-care registries are also collected in the FORCE-ACS registry.

Research questions and hypotheses with a significant focus on the secondary prevention of recurrent ischemic events are proposed. A major topic of interest is the individualization of DAPT duration based on a patient’s ischemic and haemorrhagic risk. We hypothesize that a personalized DAPT duration in patients with ACS, using the PRECISE-DAPT score and DAPT score, is superior to the current standard treatment with regards to ischemic and bleeding outcomes (see Box 1). Other research topics that will be investigated in this registry include the efficacy and safety of pharmacogenetic guided treatment for antiplatelet therapy, dual versus triple therapy in patients with an indication of oral anticoagulation, the evaluation of optimal cardiovascular risk management (in important subgroups such as the elderly and women) and patient-related outcome measures (PROMs) in patients ≥ 1 year after ACS. End points, sample sizes and statistical analyses are formed per hypothesis. Future research questions and hypotheses may be proposed as the registry progresses. All research questions and hypotheses are formulated in the research protocol (Clinicaltrials.gov; NCT03823547).

### 2.2. Study Design and Population

The FORCE-ACS registry (ClinicalTrials.gov Identifier: NCT03823547) is a multicenter, prospective registry including patients from nine non-interventional and interventional cardiac centers located in different regions of the Netherlands. The registry is coordinated by investigators at St. Antonius Hospital (Nieuwegein, The Netherlands) and the Amsterdam University Medical Center, location AMC (Amsterdam, The Netherlands). An overview of the participating institutions is provided in Table 1 and their geographic locations are shown in Figure 1. Since January 2015, consecutive adult patients (18 years or older) admitted with suspected ACS, i.e., unstable angina or non-ST-elevation myocardial infarction (NSTEMI) and ST-elevation myocardial infarction (STEMI), are prospectively included in this registry. Before May 2018, there was no legal obligation to obtain written informed consent for registries that were not subjected to the Medical Research Involving Human Subjects Act in the Netherlands. Since the enforcement of the General Data Protection Regulation (GDPR), all patients included in the registry have provided written informed consent. Patients who were included before May 2018 were contacted and asked to provide written informed consent. Patients who deceased during admission before informed consent was obtained (e.g., cardiac arrest due to ACS) will be included pseudonymously, unless objections could have been reasonably presumed. It will be encouraged to follow the current guidelines of the European Society of Cardiology (ESC) with final decisions at the discretion of the treating physician [6,15,16,17,18].

### 2.3. Data Collection

Data will be prospectively collected by members of the investigation team during admission and after 1, 12, 24 and 36 months(s) as illustrated in Figure 2. Automated data extraction from electronic medical records (EMR) will be applied as much as possible to facilitate the collection of significant amounts of data. Data extraction will be performed periodically (e.g., monthly) or, if possible, continuously from EMRs according to standardized operating procedures (SOPs). Data will be stored anonymously in a specially designed database and the input of data will be performed using a special front-end interface (REDCap, Vanderbilt University) [19]. All primary and secondary end points during an at least three-year follow-up will be recorded by the investigators, using hospital EMRs, general practitioner records, pharmacy records and patient questionnaires. Patients will be contacted at 1, 12, 24 and 36 months after discharge to ask whether they have been admitted to other hospitals and to assess their quality of life using the Short Form 12 (SF-12) and/or Seattle Angina Questionnaires [20,21]. Additionally, patients will be asked to keep track of any changes in antiplatelet regimen (e.g., temporary cessation of aspirin or P2Y_12_-inhibitor) and to provide a list of all medications they use. If necessary, this data will be supplemented with information from pharmacies.

### 2.4. Study End Points

Major end points include all-cause mortality, stroke, MI, hospital admission for ACS, stent thrombosis (classified according to the Academic Research Consortium criteria), revascularization and all bleeding requiring medical intervention, defined using different bleeding classifications (Bleeding Academic Research Consortium (BARC), Thrombolysis in Myocardial Infarction (TIMI), Global Utilization Of Streptokinase And Tpa For Occluded Arteries (GUSTO) and Platelet Inhibition and Patient Outcomes (PLATO)) [22,23]. The following end points will also be collected: mortality classification into cause of death (i.e., cardiovascular or non-cardiovascular cause of death), (temporary) cessation and duration of antiplatelet therapy after ACS and PROMs as reported in quality of life questionnaires (e.g., SF-12 and Seattle Angina Questionnaires) (see Supplementary Materials for a detailed description of all study end points). If feasible, the collection of additional relevant end points may follow as the study progresses.

### 2.5. Sample Size and Statistical Analysis

This ongoing registry is not limited to a certain size; sample sizes are calculated based on individual study hypotheses. Categorical data will be presented as number of patients and percentages. Continuous data will be presented as mean ± standard deviations, median (25th–75th percentile) or range, as appropriate. Missing data are handled on an analysis-specific basis. Event rates are estimated using the Kaplan–Meier method, and Cox proportional hazard models will be used to estimate adjusted between-group effects. Other analytical statistics are used according to individual research questions.

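### Section 2.5 names Kaplan-Meier for event rates with no exception for end points that death can preclude, so reported absolute risks of those end points will be somewhat too high

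*Protocol article*

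**What the plan says.** The general statistical plan, in section 2.5, states "Event rates are estimated using the Kaplan–Meier method", and the same sentence assigns adjusted comparisons between groups to Cox models. The next sentence leaves room for additions: "Other analytical statistics are used according to individual research questions". Section 2.1 similarly says: "End points, sample sizes and statistical analyses are formed per hypothesis".

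The end points are in section 2.4: "Major end points include all-cause mortality, stroke, MI, hospital admission for ACS, stent thrombosis", followed by revascularization and bleeding. A second list in the same section, of end points collected in addition to the major ones, includes "mortality classification into cause of death (i.e., cardiovascular or non-cardiovascular cause of death".

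Three other statements bear on mortality. Section 2.1 names "important subgroups such as the elderly and women" as groups of interest. Section 2.2 sets a lower age limit of 18 and no upper one, and section 2.3 foresees at least three years of follow-up. The Introduction cites an external registry in which "one in five ACS patients are deceased within five years".

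The article does not mention cumulative incidence functions, the Aalen-Johansen estimator or any other treatment of death as a competing event.

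**The concern.** A patient who has died can no longer have a stroke, an MI or a bleed. Kaplan-Meier applied to such an end point treats the death as ordinary censoring, as if the patient remained at risk out of sight. The resulting 1-KM estimates the risk in a hypothetical population in which nobody dies first. It is never below the proportion of patients who actually have the event, and the gap widens with mortality and with length of follow-up. The same holds for cardiovascular death, for which non-cardiovascular death competes, and the reverse.

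The registry exists to describe what happens to unselected patients, so the actual risk is the natural target. The Discussion stresses frail, older patients who are often treated conservatively, and this is where competing mortality is highest. What is at stake is the accuracy of the published absolute rates.

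**Working it through.** **Inputs**

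- Mortality: 20% at five years, from the Introduction. It comes from an external registry and is the only mortality figure in the article.
- Horizon: 36 months, the last scheduled contact in section 2.3.
- Event hazard for a non-fatal end point: 3% and 5% per year. Assumed; the article gives no rate for a single non-fatal end point.
- Constant hazards. Assumed.
- Death hazard before the event set equal to the all-cause death hazard. Assumed.
- Three-year mortality in a frail elderly subgroup: 35%. Assumed; not in the article.

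**Formulas**, with event hazard a, death hazard d and time t in years

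- 1-KM = 1 − exp(−a·t)
- Cumulative incidence (the quantity that Aalen-Johansen estimates) = a/(a+d) × [1 − exp(−(a+d)·t)]

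**Step 1: cited mortality.** d = −ln(0.80)/5 = 0.0446 per year, which implies 12.5% dead at three years.

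- a = 0.03: 1-KM = 1 − exp(−0.09) = 8.61%. Cumulative incidence = 0.03/0.0746 × [1 − exp(−0.2239)] = 0.4020 × 0.2006 = 8.06%. Excess 0.54 points, ratio 1.067.
- a = 0.05: 1-KM = 1 − exp(−0.15) = 13.93%. Cumulative incidence = 0.05/0.0946 × [1 − exp(−0.2839)] = 0.5284 × 0.2471 = 13.06%. Excess 0.87 points, ratio 1.067.

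At 24 months, an end point with 1-KM of 5% has a cumulative incidence of 4.79%, a ratio of 1.045.

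**Step 2: assumed frail subgroup.** d = −ln(0.65)/3 = 0.1436 per year.

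- a = 0.03: 1-KM is again 8.61%. Cumulative incidence = 0.1728 × 0.4059 = 7.02%. Excess 1.6 points, ratio 1.23.
- a = 0.05: 1-KM is again 13.93%. Cumulative incidence = 0.2583 × 0.4405 = 11.38%. Excess 2.6 points, ratio 1.22.

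**Step 3: range over assumed mortality.** For an end point with 1-KM of 5% at three years:

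| Mortality | Cumulative incidence | Ratio |
|---|---|---|
| 20% at five years (cited) | 4.68% | 1.07 |
| 10% per year (assumed) | 4.29% | 1.17 |
| 15% per year (assumed) | 3.97% | 1.26 |
| 25% per year (assumed) | 3.36% | 1.49 |

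**Step 4: sensitivity to the competing hazard.** Only death before the event competes. If the event itself raises later mortality, the death hazard among event-free patients is below the all-cause figure. Halving it as an illustration (d = 0.0223) gives cumulative incidences of 8.33% (a = 0.03: 0.5735 × 0.1452) and 13.48% (a = 0.05: 0.6914 × 0.1950). The excess then falls to about 3% relative. The direction does not change.

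**Step 5: does the stated sample size depend on this?** Box 1 states 5554 patients for 15% against 12% (a 20% relative reduction), α 0.05, power 0.80 and a 3:1 ratio. The two-sided pooled two-proportion formula, with p̄ = (3 × 0.15 + 0.12)/4 = 0.1425, gives for the larger group [1.960 × √(4 × 0.1425 × 0.8575) + 0.8416 × √(0.15 × 0.85 + 3 × 0.12 × 0.88)]² / 0.03² = 4145 after rounding up. Adding 1382 for the smaller group makes 5527, within 0.5% of 5554. The composite behind it contains all-cause mortality, so no death competes with it and the number stands.

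**The case against.** The strongest reply is that section 2.5 is a short default in a condensed article. It does not say that Kaplan-Meier applies to all end points, and sections 2.1 and 2.5 both let each research question bring its own methods. The choice of estimator for each secondary end point may be settled in the research protocol, which is not shown. Part of this stands: the open clauses would permit a competing-risk estimator. But they add methods without replacing the one that is named, and the sentence naming it has no exception. The point is therefore about a stated method, not about missing detail.

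A second reply is that the effect is small on the article's own mortality figure, and that the larger figures rest on assumed mortality. That stands and limits the weight of the point.

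A third reply concerns two stronger readings. A reader might infer that comparisons between groups of different age or frailty are biased. The article does not support this: adjusted between-group effects come from Cox models, which remain valid for cause-specific hazards. Nor would cumulative incidence make comparisons independent of mortality. At an equal event hazard of 3% per year it gives 8.1% and 7.0% in steps 1 and 2, where 1-KM gives 8.6% in both. The two quantities answer different questions, and only cumulative incidence answers the one about actual absolute risk. A reader might also infer that the Box 1 analysis is undermined. It is not, because its composite includes all-cause death.

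**Conclusion.** The point holds for reported absolute rates only. Applied as written, section 2.5 overstates the risk of stroke, MI, ACS admission, stent thrombosis, revascularization and bleeding. It does the same for cardiovascular and non-cardiovascular death, which section 2.4 collects in addition to the major end points.

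The direction is certain wherever some patients die before the event. The size is not. At 36 months it is about 0.5-0.9 percentage points (7% relative) under the cited mortality, constant hazards, a 3-5% yearly event hazard and all-cause mortality taken as the competing hazard. It is smaller if event-free mortality is lower, and 22-23% relative in a subgroup with an assumed 35% three-year mortality. For the average patient this is modest; for rates reported separately in elderly or frail patients it can be material.

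All-cause mortality, the Box 1 composite and its log-rank test, the 5554 patients and the Cox cause-specific hazard ratios are unaffected. The change is worth making because it is nearly free, not because any stated result fails without it.

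**What to change.** Add one sentence to section 2.5: absolute event rates for end points that are neither all-cause death nor a composite containing it are estimated by Aalen-Johansen cumulative incidence, with death as the competing event (for cause-specific death, death from the other cause).

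Keep Kaplan-Meier for all-cause death and for composites that include it. Keep the Cox models and describe them, for these end points, as cause-specific hazard models. Leave the choice of test to each research question, since a test of cause-specific hazards and a test of cumulative incidence are both legitimate.

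The cost is small. Deaths and their causes are already collected and standard software provides the estimator, so no extra patients or data are needed. The downside is that the reported rates become slightly lower than under Kaplan-Meier.

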### 2.6. Quality Control

All members of the investigation team are trained for adequate data entry with an SOP guide. Around 5–10% (randomly selected) of all baseline and clinical data and 100% of all diagnoses at discharge will be reviewed by the coordinating investigators. All major end points will be reviewed by a clinical event committee, consisting of at least two independent investigators. Furthermore, the web-based REDCap database automatically provides periodic data checks and queries for inconsistent or out-of-range data in order to urge the user to review and correct the data if needed.

### 2.7. Regulation Statement and Informed Consent

The medical ethics review committees of the various participating centers have confirmed that the Medical Research Involving Human Subjects Act does not apply to this registry. The FORCE-ACS registry will be conducted according to the Medical Treatment Agreement Act, the General Data Protection Regulation and the Declaration of Helsinki. All patients will have to provide written informed consent for participation in the registry and will have the possibility to discontinue participation at any time.

### 2.8. The FORCE-ACS Database Framework

The FORCE-ACS registry framework will enable the investigation of multiple research questions using a multitude of study designs. The registry can be used for prospective cohort studies, in which the effect of different treatment strategies may be compared and evaluated over time. Propensity matched analyses will be applied if suitable. In addition, retrospective (post-hoc) analyses can be conducted at any moment in time, depending on the availability of data for a specific research question. This will also provide valuable data for case-control studies in the future (e.g., for analysis of relatively rare complications such as stent thrombosis). The FORCE-ACS framework provides a unique foundation for multicenter registry-based randomized controlled trials (r-RCT). Since full data collection and follow-up are already performed, a randomization module can be added to enable pragmatic clinical trials. Additional data elements or biomedical data (i.e., genetic data) can be added for selected patient groups.

Box 1Evaluation of risk score-guided Dual AntiPlatelet Therapy (DAPT) duration within the Future Optimal Research and Care Evaluation in patients with Acute Coronary Syndrome (FORCE-ACS) registry.
**Risk score-guided DAPT duration**
Within the FORCE-ACS registry, a prospective, multicenter cohort study is currently being performed. Up to July 2018, DAPT duration was not determined using risk scores in any of the participating hospitals. Most patients received 12 months DAPT, which was only shortened or prolonged based on clinical judgement. From July 2018, a risk score-guided DAPT duration using the PRECISE-DAPT score and the DAPT score was encouraged in all participating centers. The cohort is divided into two groups:
Standard treatment group: DAPT duration not based on risk scoresRisk score-guided group: DAPT duration based on risk scores using the following treatment scheme (see Figure 3)ACS patients with a high bleeding risk (PRECISE-DAPT score ≥ 25) will receive a short DAPT duration (6 months); patients without high bleeding risk (PRECISE-DAPT score < 25) will receive at least 12 months of DAPT. In patients who have endured one year of DAPT without any events, patients with high ischemic risk (DAPT score ≥ 2) will receive an extended DAPT duration (at least 30 months post-ACS); in patients without a high ischemic risk (DAPT score < 2), DAPT will be discontinued after 12 months. All patients enrolled in the FORCE-ACS registry and with an indication for DAPT at discharge will be eligible for this analysis. Patients with a concomitant use of oral anticoagulants, a contraindication for aspirin or a P2Y_12_-inhibitor or implementation of a bio-absorbable vascular stent will be excluded from analysis. The primary end point for this study is defined as the composite of all-cause mortality, MI, stent thrombosis, stroke and BARC 3 or 5 bleeding at a 24 months follow-up. The expected event rate of the primary end point was estimated at 15% at a 24 months follow-up in the standard treatment group. Furthermore, we expect to enroll patients in a 3 (standard treatment) to 1 (risk score-guided treatment) ratio. Using an α of 0.05 and a 1-β of 0.80, we would need a study population of 5554 to show a relative reduction of 20% at the primary end point. We expect that approximately 10% of patients without a final diagnosis of ACS and 15% of patients with an indication for oral anticoagulation will be excluded from analysis. If the loss to follow-up is limited to 5% after 24 months, a total study population of approximately 8000 ACS patients is required. Primary analysis will compare the treatment groups from the time of inclusion to the first occurrence of any event in the composite end point using Kaplan–Meier cumulative event-free curves and formal statistical testing with the log-rank test. For measure of the treatment effect, hazard ratios will be computed with a Cox proportional hazard regression.

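### The formal primary test in Box 1 is an unadjusted log-rank test between non-randomised groups, and the adjusted analyses mentioned elsewhere are not tied to it

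*Protocol article*

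**What the plan says.** Section 2.1 sets a superiority hypothesis: personalised DAPT duration "is superior to the current standard treatment with regards to ischemic and bleeding outcomes". Box 1 describes the study meant to answer it: "a prospective, multicenter cohort study is currently being performed". On how the groups arise it says "Up to July 2018, DAPT duration was not determined using risk scores in any of the participating hospitals", and then "From July 2018, a risk score-guided DAPT duration using the PRECISE-DAPT score and the DAPT score was encouraged in all participating centers". The two groups are defined by whether DAPT duration was based on the scores.

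Box 1 fixes the primary analysis as time from inclusion to the first component of the composite, shown by Kaplan–Meier curves, with "formal statistical testing with the log-rank test". It adds: "For measure of the treatment effect, hazard ratios will be computed with a Cox proportional hazard regression". It names no covariates, strata, weights or matching.

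Two statements outside Box 1 bear on adjustment. Section 2.5, for the registry in general: "Cox proportional hazard models will be used to estimate adjusted between-group effects". Section 2.8, also in general: "Propensity matched analyses will be applied if suitable".

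**The concern.** A plain log-rank test asks whether two survival curves differ. With randomised groups, that is also a test of treatment. Here membership depends on when the patient was admitted and, after July 2018, on whether the physician or centre took up an encouraged strategy. Any difference in prognosis that follows period, centre or uptake enters the test as if it were an effect of score guidance.

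The article recognises that adjustment is needed, but places it in general statements about estimation and about study designs the registry could support. For this study the only formal test named is the crude one. If all the statements are followed, there will be a crude p-value, an adjusted hazard ratio and perhaps a matched result, with nothing to say which decides superiority if they disagree. The nominal 5% error rate and 80% power would then describe whether the curves differ. They would not describe whether score guidance works, unless the groups happen to be balanced.

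**Working it through.** **1. The plan's own figure.** Inputs from Box 1: 15% events at 24 months under standard treatment, a 20% relative reduction (so 12%), 3:1 standard to guided, α 0.05, power 0.80, total 5554. The two-sided two-proportion formula with pooled variance and no continuity correction uses p̄ = (3 × 0.15 + 0.12)/4 = 0.1425:

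n(standard) = [1.960 × √(4 × 0.1425 × 0.8575) + 0.842 × √(0.15 × 0.85 + 3 × 0.12 × 0.88)]² / 0.03² = (1.370 + 0.561)² / 0.0009 ≈ 4145

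n(guided) ≈ 1382, total about 5527. This is within 0.5% of 5554, so the stated size reproduces and is not in dispute. It is the size for an unadjusted comparison of two groups.

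**2. Precision at the planned size.**
- Events = 5554 × (0.75 × 0.15 + 0.25 × 0.12) = 5554 × 0.1425 = 791.
- SE(log HR) = 1/√(791 × 0.75 × 0.25) = 0.082.

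**3. Rejection rate with no treatment effect.** Suppose group differences alone produce an apparent hazard ratio h. The log-rank statistic is then centred at ln(h)/SE, and the two-sided rejection rate is Φ(|ln h|/SE − 1.96) + Φ(−|ln h|/SE − 1.96). The values of h are assumptions, because the documents report no imbalance or trend.

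| Assumed h | ln h | abs(ln h)/SE | Rejection rate |
|---|---|---|---|
| 1.00 | 0 | 0 | 5.0% |
| 0.95 | −0.051 | 0.62 | 9.6% |
| 0.90 | −0.105 | 1.28 | 25.0% |
| 0.85 | −0.163 | 1.98 | 50.8% |

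The result does not depend on the approximation. Recomputing the event count for each h gives 9.8%, 26% and 51%. A two-proportion version, with relative risk lowered by 5%, 10% or 15%, gives 10%, 27% and 54%.

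**4. Bias in the other direction.** The planned effect as a hazard ratio is ln(0.88)/ln(0.85) = 0.787.
- Without bias: |ln 0.787|/0.082 = 2.92, so power is about 83% on this approximation.
- With adverse confounding of 1.10: the apparent HR is 0.787 × 1.10 = 0.865, |ln 0.865|/0.082 = 1.76, so power is about 42%.

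**5. What the statements say about the primary test.**

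| Place | Scope | Role | Adjusted? |
|---|---|---|---|
| Box 1, log-rank | This study | Formal test | None stated |
| Box 1, Cox | This study | Effect measure | Not stated |
| Section 2.5, Cox | Registry in general | Estimation | Yes |
| Section 2.8, propensity matching | Registry in general | Conditional | Yes, if used |

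No row gives an adjusted formal test for this study.

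**The case against.** The strongest reply is that adjustment is planned. Section 2.5 commits the registry to adjusted Cox effects, so the Cox regression in Box 1 is plausibly the adjusted one. Section 2.8 adds propensity matching, and Section 2.1 refers to a fuller research protocol that is not shown. An article need not list covariates. All of this stands: a reader might infer that the plan ignores confounding, and the documents do not support that. It does not reach the test, however. Box 1 makes a positive choice of the log-rank as the formal test and leaves the Cox model to measure the effect.

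A second reply is that the rejection rates rest on invented bias and would apply equally to confounding left after adjustment. That also stands. The figures show how sensitive a comparison of this size is to bias. They do not show that bias exists, or that an adjusted model would be free of it. The case for adjustment is that it removes the measured part of the imbalance, which the log-rank test leaves in full.

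A third is that calling the design before/after is too simple. Groups are defined by score use, so patients after July 2018 whose duration was not score-based may belong to the standard group. This is correct, and it adds selection by uptake to the calendar difference.

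One further inference should be resisted: that propensity matching would sacrifice a known share of the standard group and its power. Section 2.8 states no matching ratio and does not tie matching to this study, so no such loss can be charged to the plan.

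**Conclusion.** The point holds as a mismatch between the named primary test and the design. As written, superiority would be decided by an unadjusted p-value from non-randomised groups, while the adjusted analyses the article foresees have no stated part in that decision. At the planned size, an assumed confounding hazard ratio of 0.90, well inside the planned effect of 0.787, would raise the chance of a significant result under no treatment effect from 5% to about 25%. Adverse confounding of 1.10 would cut power from about 83% to about 42%. These figures assume 5554 analysed patients at 3:1, the event rates in Box 1 and proportional hazards. The bias sizes are illustrative.

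Two stronger readings go beyond the documents. A reader might infer that the study's true error rate is 25% or more, but no imbalance or secular trend is reported, so the actual rate is unknown. A reader might also infer that adjustment would cure the problem. Calendar time is largely collinear with group, because no centre used the scores up to July 2018. Adjustment can therefore deal with measured case-mix and centre, but secular confounding may remain.

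**What to change.** Name one pre-specified adjusted Cox analysis as both the primary test and the primary estimate, and show the crude log-rank p-value descriptively only. One workable form is a propensity-weighted Cox model with robust variance, stratified by centre, built on baseline case-mix variables that the registry records. The variables should be listed in advance. So should a single weighting scheme, because different schemes (overlap or inverse-probability weights, for example) target different populations.

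State in the plan that calendar-time confounding is largely collinear with group and may remain after adjustment, and word the conclusion to match. A comparison limited to the early months can serve as a sensitivity check, but only an approximate one. Box 1 allows standard DAPT to be shortened on clinical judgement, so it cannot be assumed that both groups receive the same DAPT during the first six months.

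The cost is analysis-plan wording, modest programming and a little precision from weighting. A centre that contributes patients to only one group would add nothing to a centre-stratified contrast. No new patients or procedures are needed.
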